### Safety assessment

In this study, adverse events (AEs), defined as negative or unintended clinical manifestations throughout the treatment and follow-up period, will be monitored and recorded in detail on a case report form (CRF). All AEs related to the surgery, anesthesia, steroid, or analgesics, together with the soft-tissue atrophy and local infection, which might be induced by scalp infiltration with the mixture of ropivacaine and D-PAL emulsion, should be monitored during the 3 months’ follow-up. The soft-tissue atrophy, clinically manifested as superficial atrophy of skin and adipose tissue, central discoloration of the skin, yellow subcutaneous deposits, small sebaceous glands, cessation of hair growth, or mauve-colored periphery at the site of injection [36], will be monitored by careful observation and will be evaluated partly by the Patient and Observer Scar Assessment Scale (POSAS) and Wound healing score at 72 h, 1 m, and 3 months after craniotomy. AEs will be treated and reported to the Institutional Review Board (IRB) as soon as possible. Study interventions-related AEs will be treated for free. The trial will be terminated immediately in case of serious life-threatening AEs leading to prolonged hospital stay or death.

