## Data Monitoring Committee (DMC)

This trial will be monitored by an independent Data Monitoring Committee (DMC) composed of specialists in ethics, statistics, and methodology through regular interviews. The DMC will audit the assessment and collection of all data after 30%, 60%, and 100% of patient inclusions. DMC will have access to interim results. Any AE will be reported to both the DMC and the IRB for judgement. Although there are no anticipated problems that may be detrimental to the participants, serious life-threatening AEs leading to prolonged hospital stay or death will be reported and the study will be terminated immediately.

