## Statistics

All statistical analyses will be performed by a statistician who is blinded to the entire study. All analyses will include the patients completing 3 months of follow-up and will follow the intention-to-treat principle. Data analysis will be performed using SPSS 26.0 (SPSS Inc., Chicago, IL, USA). Kolmogorov-Smirnov test will be used to check for normal distribution. Normally distributed continuous variables will be described as mean ± SD and abnormally distributed variables as median (interquartile ranges, IQRs). Categorical variables will be reported as the number or proportion of patients. The primary outcome will be the pain NRS scores at 24 h postoperatively. These continuous data will be compared by independent two-tailed *t* tests if they are normally distributed or by Mann-Whitney *U* test if they are abnormally distributed. Similarly, secondary outcomes including pain NRS scores at 2, 4, 12, 48, and 72 h after craniotomy, sufentanil consumption with PCA device, PONV scores, WHOQOL-BREF, wound healing score, and POSAS scores at different time points and the duration of hospitalization will be compared by independent two-tailed *t* tests as normally distributed data or by Mann-Whitney *U* test as skewed data. In addition, the time to first button press or to first requirement of OC/PAPA will be compared by log-rank test and reported as hazard ratios (HRs) with 95% CI in Kaplan-Meier curves. Safety analyses will be compared with the incidence of AEs recorded in the safety data set using Chi-square test or Fisher’s exact test. The same statistical methods will be used for demographic characteristics and baseline information. We will judge a *P* value of less than 0.05 as significant for all tests.

Two interim analyses will be conducted for assessment of efficacy and safety after completion of the first 40 and 80 patients. The efficacy of the primary outcome and the incidence of AEs will be compared between two groups, and the study discontinuation threshold will be set at *P* < 0.01 using the alpha-sparing technique (O’Brien-Fleming) for benefit or harm.

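### The protocol ends the trial automatically on certain life-threatening adverse events, whatever their arm or cause, yet also refers every adverse event to the DMC and IRB for a decision

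*Protocol article*

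**What the plan says.** Four sections of the protocol article bear on when the trial stops for harm.

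- **Safety assessment.** "The trial will be terminated immediately in case of serious life-threatening AEs leading to prolonged hospital stay or death". Adverse events are "defined as negative or unintended clinical manifestations throughout the treatment and follow-up period", and monitoring covers "All AEs related to the surgery, anesthesia, steroid, or analgesics".
- **Data Monitoring Committee.** "Any AE will be reported to both the DMC and the IRB for judgement". The next sentence says that "serious life-threatening AEs leading to prolonged hospital stay or death will be reported and the study will be terminated immediately".
- **Statistics.** "Two interim analyses will be conducted for assessment of efficacy and safety after completion of the first 40 and 80 patients". At these looks, "The efficacy of the primary outcome and the incidence of AEs will be compared between two groups", with discontinuation at P<0.01 for benefit or harm.
- **Withdrawal criteria.** Reoperation for hematoma or brain swelling in the first 72 hours withdraws that patient. Nothing is said there about the trial as a whole.

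No section says which of these provisions prevails, and none gives an expected rate of serious events.

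**The concern.** The termination rule is stated twice, so a slip of the pen is unlikely. It does not ask which arm the patient was in, whether the event had anything to do with the infiltrated drug, how many events have occurred, or whether anyone has reviewed them. Craniotomy carries its own serious complications. A stop triggered by one of these in a ropivacaine-alone patient would say nothing about D-PAL.

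The same section that repeats the rule sends every adverse event to two bodies for a decision. If termination is automatic, those bodies have no decision to make in the cases where their judgement matters most.

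Both ways of acting on the text are poor. If the rule is followed, the trial may end before it can answer its question. If it is set aside, the protocol is breached and stopping becomes ad hoc, in a trial whose neurosurgeons know the allocation.

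**Working it through.** **1. Is the rule limited to drug-related events?** The adverse-event definition requires no link to the study drug, and the monitored causes include surgery and anesthesia. The sentence just before the termination rule in Safety assessment limits free treatment to events related to the study interventions. That qualifier was therefore at hand, and the next sentence does not use it. The text contains no relatedness condition.

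**2. Number of patients exposed.** The planned total reproduces. The inputs from Sample size are means of 2.0 and 1.2 (difference 0.8), SDs of 1.5 and 0.9, two-sided alpha 0.05 and power 90%. The unequal-variance t-test has power 0.898 with 51 per arm and 0.903 with 52, so 52 are needed. With 20% dropout, 52/0.80 = 65 per arm, or 130 in total.

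**3. Chance of at least one triggering event.** The protocol gives no rate, so the per-patient probability p is an assumption. It is taken as equal in both arms and independent between patients. If one event suffices, the chance among N patients is 1 − (1 − p)^N. For example, at p = 1% and N = 130: 1 − 0.99^130 = 0.729.

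| Assumed p | First 40 patients | First 80 | All 130 |
|---|---|---|---|
| 0.2% | 8% | 15% | 23% |
| 0.5% | 18% | 33% | 48% |
| 1% | 33% | 55% | 73% |
| 2% | 55% | 80% | 93% |

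The chance over 130 patients is 50% at p = 1 − 0.5^(1/130) = 0.53%. With 1:1 allocation and equal rates, any triggering event is as likely to fall in the control arm as in the D-PAL arm.

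**4. Distance from the comparative threshold.** For x events against none with n per arm, the two-sided Fisher P is 2·C(n,x)/C(2n,x) for x of at least 1.

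- One against none: P = 1.0 at any n.
- 20 per arm (look at 40): 7 v 0 is the first split below 0.01, with P = 0.0083.
- 40 per arm (look at 80): 8 v 0 is the first, with P = 0.0053.
- Uncorrected chi-square needs 6 v 0 and 7 v 0.

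A single event is therefore nowhere near the harm threshold. The comparison is only illustrative, because the Statistics section tests adverse-event incidence in general and not this severe subset.

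**The case against.** Several stronger readings are tempting, and the documents do not support them.

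- **That any life-threatening event ends the trial.** The event must be serious and life-threatening and must also lead to a longer stay or to death. The wording is plural as well, so a single-event trigger is one reading and not a stated rule. The probabilities above depend on that reading.
- **That early termination is likely.** This would need an event rate, and none is given. Eligibility points to lower risk: ASA I–II, age 18 to 64, elective supratentorial surgery, and exclusion of a preoperative Glasgow Coma Scale below 15. At 0.2% the chance is 23%.
- **That the rules cannot all hold.** An absolute stop for catastrophic events can coexist with a between-group threshold at two planned looks. The Statistics section does not say that P<0.01 is the only route to stopping for harm. Withdrawing a patient who is reoperated does not exclude stopping the trial, and not every reoperation would meet the trigger.

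It can also be argued that the DMC section sets a general rule (every event is judged) followed by a special case (the gravest events stop the trial), and that its remark that no harm to participants is expected hints at study-related events. The first part is a possible reading, but it still removes judgement where it matters most. The second is an inference, since neither section states a relatedness condition.

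Finally, an article may leave review procedures to the full protocol or a DMC charter. That would excuse missing detail. It does not excuse an automatic rule that is stated outright, twice.

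**Conclusion.** The point stands in limited form. The firm conflict is between automatic termination and referral to the DMC and IRB for a decision. In addition, the precedence of the automatic stop over the P<0.01 harm threshold is not stated, and its relation to the single-patient withdrawal for reoperation is left open. On a literal reading, one surgical complication unrelated to D-PAL, in either arm, could end the trial.

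How probable that is cannot be settled from the protocol. The range of 23% to 93% rests on assumed rates of 0.2% to 2%, on one event being enough, and on independence between patients. It also overstates the loss somewhat, because an event late in the trial would cost little. The columns for the first 40 and 80 patients show the part of the risk that would do most damage.

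**What to change.** Reconcile Withdrawal criteria, Safety assessment, the DMC section and Statistics, and state which rule prevails. In place of automatic termination, such events would be reported at once to the existing DMC and IRB, which judge relatedness and the balance between arms and recommend whether the trial continues. The text should also make clear how this review relates to the P<0.01 threshold at the looks after 40 and 80 patients.

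Count these events in the between-group safety comparison, including those in patients withdrawn under the withdrawal criteria. This needs saying, because Statistics restricts all analyses to patients who complete 3 months of follow-up, and a patient who dies or is withdrawn may not do so.

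The cost is protocol wording and prompt ad hoc DMC review between the scheduled audits. The DMC already receives every adverse event and has access to interim results. The Trial status section reports that recruitment had not started, so the change could be made before the first patient is enrolled.

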## Data collection and management

Data collection and management will be performed via the hospitalized medical record system or CRF by an independent researcher. All data will be kept strictly confidential for research purposes only. Only the primary investigator can obtain final test data. Follow-up will be conducted on days 1, 2, and 3 and at months 1 and 3 by an independent and experienced researcher, either in person or by contact via telephone (after discharge). Participants who discontinue or deviate from intervention protocols will not be replaced. They will be allowed to withdraw their consent without any restriction at any time. Their data will be retained, including all the primary and secondary outcomes until termination, except for the cases that are unable to complete the assessment of the primary outcome at 24 h postoperatively.

All personal information and data about the participants will be recorded into the CRFs, which are coded by an identification number and stored in a secure cabinet throughout the trial to guarantee confidentiality. All data will be entered into the Excel form for analysis by two independent researchers with double-checking. The electronic data will be stored on a double password-protected computer. Only the primary investigator and the statistician will have access to the files.

## Data Monitoring Committee (DMC)

This trial will be monitored by an independent Data Monitoring Committee (DMC) composed of specialists in ethics, statistics, and methodology through regular interviews. The DMC will audit the assessment and collection of all data after 30%, 60%, and 100% of patient inclusions. DMC will have access to interim results. Any AE will be reported to both the DMC and the IRB for judgement. Although there are no anticipated problems that may be detrimental to the participants, serious life-threatening AEs leading to prolonged hospital stay or death will be reported and the study will be terminated immediately.

### Missing data

Multiple imputations will be used to handle missing data during the whole study.

## Dissemination plans

The trial results will be made public through publication in a scientific journal.

## Statistics

All statistical analyses will be performed by a statistician who is blinded to the entire study. All analyses will include the patients completing 3 months of follow-up and will follow the intention-to-treat principle. Data analysis will be performed using SPSS 26.0 (SPSS Inc., Chicago, IL, USA). Kolmogorov-Smirnov test will be used to check for normal distribution. Normally distributed continuous variables will be described as mean ± SD and abnormally distributed variables as median (interquartile ranges, IQRs). Categorical variables will be reported as the number or proportion of patients. The primary outcome will be the pain NRS scores at 24 h postoperatively. These continuous data will be compared by independent two-tailed *t* tests if they are normally distributed or by Mann-Whitney *U* test if they are abnormally distributed. Similarly, secondary outcomes including pain NRS scores at 2, 4, 12, 48, and 72 h after craniotomy, sufentanil consumption with PCA device, PONV scores, WHOQOL-BREF, wound healing score, and POSAS scores at different time points and the duration of hospitalization will be compared by independent two-tailed *t* tests as normally distributed data or by Mann-Whitney *U* test as skewed data. In addition, the time to first button press or to first requirement of OC/PAPA will be compared by log-rank test and reported as hazard ratios (HRs) with 95% CI in Kaplan-Meier curves. Safety analyses will be compared with the incidence of AEs recorded in the safety data set using Chi-square test or Fisher’s exact test. The same statistical methods will be used for demographic characteristics and baseline information. We will judge a *P* value of less than 0.05 as significant for all tests.

Two interim analyses will be conducted for assessment of efficacy and safety after completion of the first 40 and 80 patients. The efficacy of the primary outcome and the incidence of AEs will be compared between two groups, and the study discontinuation threshold will be set at *P* < 0.01 using the alpha-sparing technique (O’Brien-Fleming) for benefit or harm.

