### Follow-up

Follow-up will last 3 months postoperatively, during which an independent researcher blinded to the patient’s group allocation will conduct the following evaluations at different time points: pain NRS, sufentanil consumption in the PCA device, time to first PCA demand button press, cumulative consumption of OC/APAP, PONV scores, wound healing scores, World Health Organization QoL abbreviated version (WHOQOL-BREF), Patient and Observer Scar Assessment Scale (POSAS) scores, etc [34]. Adverse effects related to the surgery, anesthesia, steroid, or analgesics will be monitored and documented. Follow-up will be performed by telephonic communication after discharge, at 1 and 3 months postoperatively.

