#### Primary outcome

Primary outcome will be the pain NRS scores at 24 h after craniotomy.

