### Sample size

Earlier studies have reported that incision-site infiltration with ropivacaine plus dexamethasone could reduce about 30-50% of postoperative pain severity compared with ropivacaine alone [6, 19, 22]. Based on these literatures and our clinical experience, we hypothesize that the pain NRS scores was approximately 2.0 ± 1.5 (mean ± standard deviation) scores in the ropivacaine alone group and attempt to detect a difference of 40% in pain NRS scores between groups at 24 h after craniotomy. Therefore, the pain scores would be about 1.2 ± 0.9 scores in D-PAL plus ropivacaine group at 24 h after craniotomy. PASS V.11 software (NCSS, Kaysville, UT, USA) is used for sample size calculation with *α* = 0.05, *β* = 0.1, and power = 90%. Considering a dropout rate of 20%, a total of 130 patients will be required in this trial (*n* = 65 per group).

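### The Statistics section analyses a 24 h primary outcome in 3-month completers and calls it intention-to-treat, which conflicts with the rule for retaining withdrawn patients' data

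*Protocol article*

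**What the plan says.** Five parts of the protocol article bear on who enters the primary comparison.

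- **Primary outcome:** "Primary outcome will be the pain NRS scores at 24 h after craniotomy".
- **Follow-up:** "Follow-up will last 3 months postoperatively".
- **Statistics:** "All analyses will include the patients completing 3 months of follow-up and will follow the intention-to-treat principle". This is the only sentence that says who is analysed, and it covers the primary outcome as well as the later ones.
- **Data collection and management:** "Participants who discontinue or deviate from intervention protocols will not be replaced". It then says "Their data will be retained, including all the primary and secondary outcomes until termination", with one exception: "except for the cases that are unable to complete the assessment of the primary outcome at 24 h postoperatively".
- **Missing data:** "Multiple imputations will be used to handle missing data during the whole study".

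The Withdrawal criteria add the events that take a patient out of the study. Some can only happen on the day of surgery (a short operation, delayed waking or extubation). Some can happen at any time up to 72 h (reduced GCS, poor cognition, high fever, certain revisions). Others have no time limit within follow-up (unplanned radiotherapy or chemotherapy, loss to follow-up, voluntary withdrawal).

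**The concern.** Intention-to-treat means that patients are analysed as randomised, whatever happens afterwards. Completing 3 months is something that happens afterwards, so one sentence asks for two incompatible sets. The conflict matters because the primary score is fixed at 24 h. A patient who gives that score and is lost in the second month has contributed everything the primary comparison needs, yet the Statistics section leaves that patient out.

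Two things are at stake. First, if late loss is related to both arm and pain, dropping these patients biases the comparison. Second, the analysis rule and the retention rule point to different patients, so the population could be settled after the data are seen, and a completer result could be reported under the intention-to-treat label.

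**Working it through.** **1. The rules side by side, for three kinds of patient**

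| Patient | Statistics | Data collection and management | Missing data |
|---|---|---|---|
| 24 h score recorded, reaches 3 months | analysed | kept | gaps at other times imputed |
| 24 h score recorded, leaves later | not analysed, yet intention-to-treat is claimed | kept | later values imputed |
| Leaves without a 24 h score | not analysed, yet intention-to-treat is claimed | not kept | 24 h score would be imputed |

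The second row is the main conflict. The third row is the narrower one: if cases without a 24 h assessment are removed, no missing primary score remains to be imputed.

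**2. Reproducing the sample size**

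Inputs from Sample size: control 2.0 (SD 1.5), experimental 1.2 (SD 0.9), difference 0.8, α = 0.05, power 90%, dropout 20%. The test is two-sided (Statistics) and allocation is 1:1 (Study design).

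- Sum of variances: 1.5² + 0.9² = 2.25 + 0.81 = 3.06.
- Normal approximation: n = 3.06 × (1.960 + 1.282)² / 0.8² ≈ 50.2, so 51 per arm.
- Noncentral t (pooled or Welch): 52 per arm.
- With dropout: 52 / (1 − 0.20) = 65 per arm, 130 in total.

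The stated 130 is reproduced. The plan therefore already expects to analyse 52 per arm.

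**3. Power with and without the late leavers**

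Noncentrality = 0.8 / √(3.06 / n), Welch degrees of freedom, two-sided 0.05.

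| Per arm with a 24 h score | Noncentrality | Power |
|---|---|---|
| 52 (all 20% lost) | 0.8 / 0.2426 = 3.30 | 90.3% |
| 58 (7 of 13 lost before 24 h) | 0.8 / 0.2297 = 3.48 | about 93% |
| 60 (5 of 13 lost before 24 h) | 0.8 / 0.2258 = 3.54 | 93.9% |
| 65 (none lost before 24 h) | 0.8 / 0.2170 = 3.69 | 95.5% |

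The planned loss is 0.20 × 130 = 26 patients. The documents do not say how many of these losses come after 24 h, so 26 patients and 95.5% are upper bounds, and the two middle rows are illustrations.

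**4. What bias could look like (assumption only)**

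Suppose a fraction q of an arm is left out and those patients' 24 h NRS is higher by D than in the patients kept. The arm's full mean is then the retained mean plus q × D. With the same D in both arms, the between-group difference is off by (difference in q) × D.

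- Loss differing by 10 percentage points (for example 15% and 25%, which average 20%), D = 1: 0.10 × 1 = 0.10 points, and 0.10 / 0.8 = 12.5% of the target difference.
- The same, D = 2: 0.10 × 2 = 0.20 points, and 0.20 / 0.8 = 25%.
- Equal loss and equal D in both arms: no bias.

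Neither the 10-point imbalance nor the 1 to 2 point gap comes from the documents.

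**The case against.** **The wording does not say only.** True, and the retention rule taken alone would keep these patients' data. But a sentence that defines who is in all analyses by naming completers has no other natural reading, and a retention rule does not decide who is analysed. The disagreement is itself the defect.

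**A full protocol or SAP would settle it.** The article does not leave the population unstated. It states rules that conflict, and a later document would have to override published text.

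**The sample size allows for the loss.** This stands: "Considering a dropout rate of 20%, a total of 130 patients will be required in this trial". A reader might infer that the completer rule leaves the trial underpowered. It does not, because 52 per arm meets the stated 90%. What is given up is possible surplus power.

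**Not all losses are caused by this rule.** This also stands. A reader might infer that 26 patients with valid scores would be thrown away. Some withdrawal criteria act on the day of surgery and others may act before 24 h, so part of the 26 may have no 24 h score under any analysis set.

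**Imputation still has a use among completers.** Correct. A patient who reaches 3 months can lack a 4 h or 12 h NRS, a PONV score or questionnaire items. It would be wrong to say that the imputation rule is pointless, or that it defines a third analysis population. The clash is limited to the missing 24 h score. Even there, the exception could be read as covering only patients who discontinue or deviate, which would leave imputation for a patient who stays in the study but misses the assessment.

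**Late loss related to arm is unlikely.** Patients and follow-up researchers are blinded, and patients likely to need radiotherapy or chemotherapy are excluded at entry. Both lower the risk. Neither removes it: the surgeons know the allocation, and the Discussion links perioperative dexamethasone to infection and to less pain.

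**Conclusion.** The Statistics sentence is wrong as written and should be corrected before recruitment. A 3-month completer set is not intention-to-treat, it leaves out patients with a recorded 24 h score because of later events, and it conflicts with the rule that retains their data. The exception for cases without a 24 h assessment further conflicts with multiple imputation of the primary outcome.

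The damage is to validity: possible bias, and freedom to choose the population later. It does not cause a shortfall in power. At the planned 20% loss, at most 26 of 130 patients are affected, and power could rise from 90.3% to at most 95.5% on the plan's own means and SDs.

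A reader might take the 0.1 to 0.2 point bias as an estimate. The documents give no basis for that. It illustrates the mechanism under an assumed imbalance in loss and an assumed pain gap, and the finding does not depend on it.

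**What to change.** 1. **Statistics:** replace the completer sentence with a statement that the primary analysis includes all randomised patients in their allocated arm, uses every recorded 24 h NRS whatever happens later, and multiply imputes missing 24 h scores as the Missing data section provides.
2. **Data collection and management:** delete the exception for cases without a 24 h assessment.
3. **Withdrawal criteria:** state that meeting a criterion does not remove data already recorded, and that the 24 h NRS is still collected where the patient can be assessed and consents. Without this, patients withdrawn on the day of surgery would enter the primary analysis as imputed values.
4. **Secondary outcomes:** analyse them in all randomised patients at their own time points, with the same multiple imputation, so that no new conflict with the Missing data section arises.
5. **Sensitivity analysis:** keep the 3-month completers for this purpose only, and label them as completers.

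The cost is wording, plus continued 24 h assessment of some withdrawn patients at a visit already scheduled. The sample size stays at 130. The article gives the trial status as not yet recruiting, so the change can be made before any data exist.

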### Randomization and blinding

Randomization sequence will be generated by a designated staff not involved in outcome data collection and analysis, who will use the block randomization method via SPSS version 22.0 (International Business Machines Inc., USA), with an electronic table of random numbers to allocate eligible participants to either of the two groups (in a 1:1 ratio). The allocation sequences will be prepared and be kept inside sealed, opaque, and consecutively numbered envelopes. The envelope will be opened by the neurosurgeons in charge, who will then prepare the study solution based on the respective allocation scheme and be therefore made aware of group assignations. Participants will be enrolled by a dedicated research nurse not involved in the data collection and analysis, and the neurosurgeons in charge are responsible for assigning participants to interventions. This is an open-label design with only patients and independent researchers in charge of follow-up and data analysis blinded to allocation. The D-PAL is a lipid emulsion in the infiltration solution, which can be easily distinguished from the clear ropivacaine alone study solution. Therefore, unblinding will not occur.

Prior to the commencement of the study, all investigators will receive standardized training on trial content, treatment strategies, evaluation, and quality control. All interventions will be carried out in accordance with clinical practice guidelines. During preoperative visit, eligible patients should be acquainted with pain NRS ranging from 0 (no pain) to 10 (worst possible pain) [31]. They will be guided on how to use a patient controlled analgesia (PCA) device.

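### A Kolmogorov-Smirnov gate chooses the primary test, and the branch it will almost certainly select is not the one that the 90% power was computed for

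*Protocol article*

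**What the plan says.** The Primary outcome section reads: "Primary outcome will be the pain NRS scores at 24 h after craniotomy". The Randomization and blinding section describes the scale as "pain NRS ranging from 0 (no pain) to 10 (worst possible pain" and does not say whether only whole numbers are recorded.

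Under Statistics, "Kolmogorov-Smirnov test will be used to check for normal distribution". The primary outcome is then compared by "independent two-tailed *t* tests if they are normally distributed or by Mann-Whitney *U* test if they are abnormally distributed". The same section describes normal variables by mean and SD and the others by median and interquartile range. It does not say whether normality is checked in each arm or in the pooled data, or whether the critical value allows for an estimated mean and SD (the Lilliefors correction).

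Under Sample size, the planning assumption is that "the pain NRS scores was approximately 2.0 ± 1.5 (mean ± standard deviation) scores in the ropivacaine alone group" and that "the pain scores would be about 1.2 ± 0.9 scores in D-PAL plus ropivacaine group at 24 h after craniotomy". With α = 0.05, 90% power and 20% dropout, the total is 130, or 65 per group. No power or sample size is given for the Mann-Whitney branch.

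**The concern.** The planning means lie within about 1.3 SDs of the floor of the scale (2.0/1.5 and 1.2/0.9 are both 1.33). Whole-number scores with those means and SDs fall on a handful of values near zero, and a Kolmogorov-Smirnov test with about 52 patients per arm readily detects that lumpiness. The plan's own assumptions therefore come close to settling the result of its gate before any data arrive, and they point to the rank test.

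The power statement belongs to the other branch. Mann-Whitney responds to the ordering of scores rather than to the difference in means, and the assumed arms differ in spread as well as in location. Its power for the same means and SDs thus depends on a distribution shape that the article does not give. At stake is whether the trial has the 90% power it claims for its primary comparison.

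**Working it through.** **Inputs.** From Sample size: means 2.0 and 1.2, SDs 1.5 and 0.9, α = 0.05, power 90%, dropout 20%, 65 per arm. From Statistics: two-tailed tests and the Kolmogorov-Smirnov gate. Assumed, because the article does not say: whole-number recording, the score shape, and how the normality test is applied.

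**Step 1: reproduce the stated size.** For two means with unequal SDs,

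n per arm = (1.96 + 1.2816)² × (1.5² + 0.9²) / 0.8² = 10.507 × 3.06 / 0.64 = 50.2, so 51.

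With the noncentral t distribution (Welch), power is 0.898 at 51 and 0.903 at 52, so 52 per arm. Allowing for dropout, 52 / 0.8 = 65 per arm, or 130. The stated figure is reproduced exactly as a comparison of means. Sizing for Mann-Whitney by its usual efficiency of 0.955 would give 52 / 0.955 = 54.5, so 55 evaluable and 55 / 0.8 = 68.75, so 69 per arm, which is not the stated number.

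**Step 2: which branch will run?** I simulated whole-number 0-10 scores matched to the planned means and SDs, 52 per arm.

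- Lilliefors critical value: normality rejected in at least 99.8% of trials in each arm, and in 100% when either arm or the pooled data count.
- Uncorrected critical value: rejected in at least 99.8% of trials in at least one arm, and in 100% of trials when pooled.
- Uncorrected, control arm alone: rejected in only about 28% of trials for near-normal shapes, rising to nearly 100% for skewed ones.

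**Step 3: power of each test at 52 evaluable per arm**, two-sided 0.05, Mann-Whitney corrected for ties:

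| Shape (whole numbers) | Welch t | Mann-Whitney |
|---|---|---|
| Rounded normal | 0.91 | 0.80 |
| Discrete maximum entropy | 0.91-0.92 | 0.80 |
| Rounded gamma | 0.92-0.93 | 0.86-0.87 |
| Rounded lognormal | 0.93 | 0.93-0.94 |

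Adding less regular shapes, including ones with extra zeros, widened the ranges to about 0.71-0.95 for Mann-Whitney and 0.88-0.94 for the t test. With decimal scores Mann-Whitney gave about 0.87 (normal) and 0.88 (gamma).

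**Step 4: sensitivity to dropout.** If all 65 per arm were evaluable, Mann-Whitney power would be about 0.88 (rounded normal and maximum entropy), 0.93 (gamma) and 0.97 (lognormal).

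**Step 5: size of the gap in patients.** Mann-Whitney needs about 70 evaluable per arm for 90% power under the rounded normal (70 / 0.8 = 87.5, so 88 per arm, 176 in total). Under the rounded gamma it needs about 58 (58 / 0.8 = 72.5, so 73 per arm, 146 in total).

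**The case against.** The strongest reply is that nothing here is invalid. Mann-Whitney suits a bounded ordinal score. With identical distributions in the two arms at 52 each, both tests held a type I error of 0.048-0.049. If the gate nearly always gives the same answer, it also leaves little room for choosing a test by its result. All of that stands: the point concerns power and consistency, not bias, and a reader should not infer that the primary result would be unsound.

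The size of the shortfall also rests on assumptions outside the document. Whole-number recording is usual but not stated, and no score shape is given. Right skew is at least as plausible as a near-normal shape with a mean of 2.0, an SD of 1.5 and a floor at 0, and under the rounded lognormal Mann-Whitney does as well as Welch. Fewer dropouts would help too. It would therefore be too strong to say that power falls below 90% for most plausible shapes: the document gives no basis for ranking them.

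Two other strong readings fail. One is that the t test can never be used: with an uncorrected critical value the control arm alone often passes, and the article does not fix the rule. The other is that the mean difference would never be reported: the article plans medians and interquartile ranges for skewed data, but it does not exclude a mean difference, and detail on effect estimates may sit in a fuller document.

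What remains is that the article itself fixes the gate and both branches, and quotes power that fits only one of them.

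**Conclusion.** The point holds in a limited form. The 130 patients and 90% power come from a comparison of means, while the primary test is left to a normality check. Given whole-number scores and either the Lilliefors correction, pooling or an either-arm rule, that check will almost certainly select Mann-Whitney. Its power at 52 evaluable per arm is then about 80% to 94% across the four main shapes. At the lower end the type II error is 20%, twice the stated 10%; at the upper end nothing is lost. With decimal scores the shortfall is only 2 to 3 percentage points. Welch gives about 91-93% on the same four shapes. The stated 90% is thus not reliably delivered by the analysis as planned, though it may be reached under strong right skew or with few dropouts.

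**What to change.** Remove the Kolmogorov-Smirnov gate for the primary outcome and name one test in advance. Either choice is defensible:

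- **Means.** Make the difference in mean 24 h NRS, with 95% CI by Welch t test, the primary analysis and Mann-Whitney a sensitivity analysis. This matches the existing sample size and power.
- **Ranks.** Keep Mann-Whitney as the primary test and restate its power as about 80-94% at 52 evaluable per arm, depending on shape, with the shape assumptions named.

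State also whether NRS is recorded in whole numbers. The change is about two sentences and needs no extra patients or data. The first option costs one added sensitivity analysis; the second, a less favourable power statement. The article gives the trial status as not yet recruiting, so the choice can be made before any outcome data exist.
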